## Abstract

**Background:**

Chronic itch significantly affects patients’ quality of life. Acupuncture shows therapeutic potential for chronic itch, while its neural mechanisms remain unclear. This study aims to investigate the immediate anti-itch effects of acupuncture in patients with chronic itch and explores the underlying neural mechanisms through functional near-infrared spectroscopy (fNIRS) monitoring.

**Methods:**

This study is a randomized controlled design. A total of 40 participants with chronic itch will be randomly assigned to the verum acupuncture group or the sham acupuncture group. The fNIRS will be used to monitor hemodynamic activity and functional connectivity of the prefrontal cortex and motor areas. The data will be continuously acquired across three consecutive 5-min epochs: (1) pre-stimulation baseline (5 min before needle insertion), (2) intra-stimulation phase (during 5-min needle retention), and (3) post-stimulation observation (5 min immediately after needle withdrawal). The primary outcome is the change in itch numeric rating scale score, secondary outcomes include the degree of itch relief, immediate comfort, intensity of itch, deqi intensity scale and expectation of therapeutic effect. In addition, both regional brain activation and functional connectivity will be analyzed.

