### Outcomes

The assessment will be conducted before and after the treatment, and the assessment time points are presented in Table 1.

**Table 1 tab1:** Data collection schedule for clinical assessments.

Research phase	Pre-acupuncture resting state	Intervention period	Post-acupuncture resting state
Timepoint	5 min before needle insertion	During the needle retention period	5 min immediately after needle withdrawal
Medical history			
Signed informed consent	✓		
Inclusion/exclusion criteria	✓		
Demographic & baseline data			
Demographic questionnaire	✓		
Past medical history	✓		
Concomitant treatments	✓		
Psychometric scales			
Self-Rating Depression Scale	✓		
Pittsburgh Sleep Quality Index	✓		
Generalized Anxiety Disorder-7	✓		
Clinical assessments			
Degree of itch Relief		✓	
Itch intensity	✓	✓	✓
Immediate comfort level		✓	
Treatment expectancy	✓		
Treatment credibility scale		✓	
Deqi intensity scale		✓	
Trial evaluation			
Adverse events record			✓
Physician/Patient Global Assessment			✓
Blinding assessment			✓

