#### Primary outcomes

The primary outcome was defined as the change of the itch NRS score, calculated by subtracting the post-intervention score from the baseline score. The intensity of itch will be evaluated using the NRS. The NRS is a patient-reported instrument in which subjects rate their subjective itch intensity on a numerical scale anchored at 0 (“no itch”) and 10 (“worst imaginable itch”). Measurements will be conducted at pre-acupuncture resting state, intervention period, and post-acupuncture resting state.

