### Expectation and credibility

Before the first treatment session, the expectation questionnaire will be used to assess the patients’ expectations. Expectation will be measured using the NRS scale, where 0 indicates complete lack of expectation and 10 signifies the maximum expectation. After the final treatment session, the credibility questionnaire will be used for assessment. The credibility scale assesses acupuncture-induced confidence change in itch relief using a 5-point scale ranging from −2 to 2, where −2 indicates “marked decrease,” −1 indicates “mild decrease,” 0 indicates “no change,” 1 indicates “mild increase,” and 2 indicates “marked increase.”

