### Statistical analysis

All statistical analyses will be performed using the IBM SPSS Statistical software package version 26 (IBM, Chicago, IL, USA). All the numerical data will be presented in the form of average values and standard deviations, and will be analyzed using the independent t-test or Mann–Whitney U test. The categorical data will be expressed as number (n) and percentage (%), and the differences between groups will be compared using the Chi-square. The preprocessing and analysis of fNIRS data will be carried out using NirSpark (Danyang Huichuang Medical Equipment Co. Ltd., China).

A two-sample *t*-test will be conducted to compare the brain activation and functional connectivity between the verum acupuncture and the sham acupuncture groups. All statistical tests will use a significance level of 0.05, with corrections for multiple comparisons.

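### Expectation is measured only before needling, so it is a baseline characteristic and not a secondary outcome; separately, the unadjusted primary test is valid but leaves collected baseline data unused

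*Protocol article*

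**What the plan says.** **Outcome list.** The abstract (Methods) states that "secondary outcomes include the degree of itch relief, immediate comfort, intensity of itch, deqi intensity scale and expectation of therapeutic effect".

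**Timing of expectation.** The section Expectation and credibility states: "Before the first treatment session, the expectation questionnaire will be used to assess the patients’ expectations". Table 1 (Outcomes) has a row "Treatment expectancy" with one tick, in the pre-acupuncture column, and none during or after needling. The Discussion describes a single session, so no later session could supply a second rating.

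**Scale.** "Expectation will be measured using the NRS scale, where 0 indicates complete lack of expectation and 10 signifies the maximum expectation".

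**A neighbouring but different measure.** "After the final treatment session, the credibility questionnaire will be used for assessment". This is a separate five-point scale of change in confidence, and it is not in the abstract's list.

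**Place in the body.** The text under Secondary outcomes describes itch relief and deqi. Expectation has its own heading further on.

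**Primary outcome and analysis.** "The primary outcome was defined as the change of the itch NRS score, calculated by subtracting the post-intervention score from the baseline score". For numerical data, the Statistical analysis section says that they "will be analyzed using the independent t-test or Mann–Whitney U test". It names no covariate.

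**The concern.** Two separate matters meet here.

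The first is classification. An outcome has to be something that treatment could alter. A rating completed before the needle goes in cannot be altered by it. In randomised arms the null hypothesis for such a variable is true by design, so a p-value below 0.05 says nothing about acupuncture. If expectation stays on the outcome list and receives the general test for numerical data, a chance difference could be reported as a finding.

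The second is efficiency. The primary outcome is a self-rated 0–10 score, and the trial plans 20 patients per arm. Baseline itch NRS and expectation are both collected before needling, yet the stated analysis uses neither as a covariate. If either predicts the change in itch, a model containing it estimates the treatment effect more precisely from the same patients.

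**Working it through.** **1. Timing.** Three places set side by side:
- Abstract: expectation is among the secondary outcomes.
- Expectation and credibility: it is rated before treatment.
- Table 1: one tick, pre-acupuncture column only.

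The last two agree with each other and are incompatible with the first.

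**2. What a between-group test of expectation would show.** In 100,000 simulated trials with 20 per arm, a normally distributed pre-treatment variable and a two-sided t-test at 0.05, the rejection rate was 5.1%. This is the nominal error rate and nothing more.

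**3. The plan's own sample size.** The inputs come from the Sample size section: mean changes 2.86 and 2.00, SDs 1.07 and 0.58, power 80%, significance level 5% (two-sided assumed, as the section does not say), dropout 20%.
- Difference: 2.86 − 2.00 = 0.86.
- SD: √[(1.07² + 0.58²)/2] = 0.861, so d = 0.86/0.861 = 0.999.
- Normal approximation: n = 2 × (1.960 + 0.842)² / 0.999² = 15.7, hence 16 per arm.
- With dropout: 16/0.80 = 20 per arm, as stated.

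The exact noncentral t calculation gives 16.7, hence 17 per arm before dropout. That small difference does not affect this point.

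**4. Power of the stated, unadjusted test.** Completers: 20 × 0.80 = 16 per arm. Standard error: 0.861 × √(2/16) = 0.304. Noncentrality: 0.86/0.304 = 2.83 on 30 degrees of freedom. Power is 78.1%.

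**5. Power with one baseline covariate.** Let r be the within-arm correlation between the covariate and the change in NRS. The article gives no value, so r is an assumption and is shown over a range.
- Residual SD: 0.861 × √(1 − r²).
- Standard error: residual SD × √(2/n) × √(1 + 1/(2n − 4)). The last factor allows for chance covariate imbalance; at n = 16 it is √(1 + 1/28) = 1.018.
- Degrees of freedom: 2n − 3 = 29, against 30 unadjusted.
- Worked case, r = 0.3: residual SD 0.821, standard error 0.295, noncentrality 2.91, power 80.3%.

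| Assumed r | Power with one covariate | Difference from 78.1% |
|---|---|---|
| 0 | 76.6% | −1.5 points |
| 0.1 | 77.0% | −1.1 |
| 0.2 | 78.2% | +0.1 |
| 0.3 | 80.3% | +2.2 |
| 0.4 | 83.4% | +5.3 |
| 0.5 | 87.3% | +9.2 |

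Break-even is near r = 0.2. The table applies to one covariate. With two, what counts for expectation is its correlation with the change beyond what baseline NRS already explains, and that too is unknown.

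**The case against.** **The body already keeps expectation apart.** It is not described under Secondary outcomes, so the error may be one phrase in the abstract. This stands, and it makes the first part a small correction. It remains a correction: the abstract states an outcome list that the measurement schedule cannot support.

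**The unadjusted test is valid, and covariates are commonly left to an analysis plan that is not shown.** Both are true. A reader might infer that the primary analysis is wrong without expectation in it. The article does not support that, since randomisation protects the comparison. What the article does do is name the test, and a more efficient one is available from data already collected. That is a recommendation about method and not an error in the stated test.

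**A chance imbalance in expectation.** A reader might infer that, left unadjusted, it biases the result. It does not. With 20 per arm, a one-SD imbalance shifts the estimate by r × √(2/20) × 0.861, which is 0.08 to 0.14 NRS points for an assumed r of 0.3 to 0.5. That shift is part of ordinary sampling error and is already inside the t-test's standard error of 0.861 × √(2/20) = 0.27.

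**Multiplicity.** A reader might also infer that removing expectation spares a test in the corrected family. The Statistical analysis section mentions correction for multiple comparisons only in general terms, directly after the brain activation and connectivity tests. It defines no family and does not say that expectation belongs to one.

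**Adjustment can lose power.** This stands: about 1.5 points if the covariate predicts nothing.

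**Conclusion.** The misclassification is plain from the article itself: expectation is listed as a secondary outcome and is measured only before needling. It is a baseline characteristic and cannot show a treatment effect. The consequence is minor, and neither the definition of the primary outcome nor the sample size is affected.

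The stated primary analysis is valid but not the most efficient choice. One baseline covariate would change power by between −1.5 and +9.2 points as r runs from 0 to 0.5. These figures rest on the pilot means and SDs, a two-sided 5% level, 16 completers per arm, a common residual SD and an assumed r. They support prespecifying adjustment as an improvement, most directly for baseline NRS, which enters the change score by construction. They do not show that expectation must be in the primary model.

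One condition applies to expectation. The article places the rating before needling but does not say whether it precedes disclosure of the allocation. A baseline covariate should be recorded before allocation is known.

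**What to change.** 1. Remove expectation from the secondary outcomes in the abstract, so that it agrees with Table 1 and the body. Report it by arm as a baseline characteristic without a between-group test. Cost: wording only.
2. Prespecify a linear model (ANCOVA) for the primary change in itch NRS, with treatment group and baseline NRS as terms, in place of the choice between t-test and Mann–Whitney test. Cost: one degree of freedom, and a small loss of power if r is below about 0.2.
3. Add expectation as a further covariate, stating in advance whether in the primary or a supportive model, provided it is recorded before allocation is known. State that order explicitly. Cost: one more degree of freedom, two in all.

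No new data are needed, because both values are already in the schedule.

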**Discussion:**

This study plans to observe the immediate anti-itch effects of acupuncture for patients with chronic itch and reveal associated brain functional changes using fNIRS. The findings will provide a neurobiological basis for the anti-pruritic mechanisms of acupuncture.

**Clinical trial registration:**

http://itmctr.ccebtcm.org.cn/, identifier ITMCTR2025001506.

## Introduction

Itch, an unpleasant sensory experience, fundamentally arises from the activation and central processing of specific neural pathways in the brain (1, 2). Chronic itch is defined as itch that persists for more than 6 weeks (3). The 2023 Global Burden of Disease Database indicates that approximately 10.84 million individuals worldwide are affected by pruritus-related diseases (4). A cohort study by Matterne et al. demonstrated that the prevalence of chronic itch can be as high as 25% (5). Chronic itch commonly causes emotional distress, sleep disturbances, and difficulties in performing daily activities, thereby substantially compromising patients’ mental and social well-being as well as their overall quality of life (6–8). The pathogenesis of chronic itch involves dysregulated signaling across multiple systems, ranging from the skin barrier and immune cells to peripheral nerve fibers, spinal cord, and brain regions (9). Currently, no medications are Food and Drug Administration approved specifically for the treatment of chronic itch (10). The conventional management of chronic itch in clinical practice relies on symptom-targeted agents such as antihistamines, corticosteroids, and immunosuppressants (11). Nevertheless, these approaches are associated with notable limitations, including suboptimal efficacy and significant adverse effects from prolonged administration (11), Thus driving the need for novel therapeutic strategies.

Acupuncture has been widely applied in the management of itch (12–15). Meta-analysis of Wei et al. has shown that acupuncture resulted in a greater reduction in itch scores in comparison to loratadine or sham acupuncture controls (16). Du et al. reported that acupuncture combined with bloodletting therapy was significantly more effective than oral loratadine in reducing itch (17). In a meta-analysis, Lu et al. found that itch scores in the acupuncture plus traditional Chinese medicine group were significantly lower than those in the conventional western medicine group (18). Similarly, the research conducted by Shi et al. indicated that acupuncture therapy was significantly more effective than oral cetirizine hydrochloride in alleviating patients’ itching symptoms (13). Our previous studies also demonstrated that acupuncture significantly alleviated itch in patients with chronic spontaneous urticaria (19, 20). Although the sustained therapeutic effects of acupuncture have been documented, a critical knowledge gap remains: the immediate central effects of acupuncture during needling and their underlying cortical mechanisms in chronic itch patients are still poorly understood.

Chronic itch drives central sensitization, a state of neuronal hyperexcitability in the spinal cord and brain, leading to a heightened and exaggerated response to itch stimuli (21). Conversely, brain activity also influences chronic itch. In a mouse model of atopic dermatitis, Zhanmu et al. (22) established a role for the medial prefrontal cortex (mPFC) in itch processing, showing that kainic acid-induced lesions of this region significantly attenuated scratching behavior.

Neuroimaging modalities have been widely used to elucidate central mechanisms underlying itch, providing critical insights into cortical and subcortical processing of pruriceptive signals (23, 24). A functional magnetic resonance imaging (fMRI) study found that the functional connectivity of the right orbitofrontal cortex (OFC), medial prefrontal cortex, and premotor cortex in patients with chronic spontaneous urticaria was more deactivated than in healthy individuals (25). To investigate the mechanisms underlying itch sensation, Li et al. used near-infrared spectroscopy to monitor the dynamic changes of cortical oxygenated hemoglobin (HbO) and deoxygenated hemoglobin (HbR) concentrations in healthy subjects during histamine-induced itch, and the results demonstrated that multiple channels corresponding to Brodmann areas in the frontal cortex were activated (26).

Functional neuroimaging has greatly advanced our knowledge of itch-related brain activity, yet most studies rely on fMRI, which is costly, less tolerant to movement, and unsuitable for real-time monitoring during acupuncture. In contrast, functional near-infrared spectroscopy (fNIRS) provides a non-invasive, motion-tolerant, and temporally sensitive method for monitoring dynamic cortical hemodynamic changes during treatment (27, 28). This technique offers real-time monitoring, high time resolution and simple operation (29), and demonstrates robustness against motion interference and the ability to capture reliable data even during spontaneous itch (30).

Therefore, based on prior evidence (22, 25), we hypothesize that acupuncture’s immediate antipruritic effect correlates with modulation of cortical regions involved in itch processing, particularly the mPFC, OFC, and premotor cortex, which can be captured in real-time by fNIRS. The term “immediate effect” refers to the rapid, short-term modulation of symptoms observed shortly after a single acupuncture intervention. Thus, this study aims to characterize acupuncture’s immediate effect and corresponding cortical response using fNIRS technology.

## Methods

### The study design

This prospective randomized controlled trial will be conducted at the Pidu District Hospital of Traditional Chinese Medicine in Chengdu. Participants will be recruited through posters and the outpatient department of dermatology from August 1 to December 31, 2025. This trial has been approved by the Ethics Review Committee of Chengdu, Pidu District Traditional Chinese Medicine Hospital (K-2025-047), and registered on the http://itmctr.ccebtcm.org.cn/ (ITMCTR2025001506).

### Study population

#### Eligible criteria

Inclusion criteria are as followed: (1) Participants should have a clear dermatological diagnosis, such as chronic urticaria (31), atopic dermatitis (32), psoriasis (33), or neurodermatitis (34). (2) Right-handed participants, aged 18 to 60, with a minimum of a primary school education, with no restriction on gender. (3) Participants with a duration of itch ≥ 2 months and an average Numerical Rating Scale (NRS) score ≥ 4 over the past week, daily occurrence of itch, and relatively stable itch intensity over the preceding 2 weeks.

Exclusion criteria are listed below: (1) Participants with severe mental illness (e.g., schizophrenia, bipolar disorder) or cognitive impairment. (2) Participants who are administrated with any medication known to influence chronic itch symptoms in the 2 weeks prior to enrollment. (3) Participants with contraindications for acupuncture treatment (such as bleeding tendency or localized infection at acupoints, hemophilia). (4) Pregnant or lactating women; patients with skin infections or other acute dermatological conditions. (5) Participants with severe hepatic/renal dysfunction or cardiopulmonary diseases. (6) Participants with a history of alcohol abuse or substance use disorders. (7) Participants unable to cooperate with the fNIRS examination. (8) Participants who have received acupuncture treatment for itch within the past 6 months.

#### Sample size

Based on the observed change in itch NRS (numeric rating scale) scores from the pilot experiment (verum acupuncture group: 2.86 ± 1.07 VS sham acupuncture control group: 2.00 ± 0.58). With 80% statistical power, a 5% significance level, and accounting for a projected 20% dropout rate. Each group requires 20 people, and a total of 40 subjects need to be recruited. The calculation was performed using an *a priori* power analysis conducted with G*Power software (version 3.1), based on a t-test for the difference between two independent means (35).

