#### Randomization and allocation concealment

The random numbers will be generated using SPSS 26.0 software. An independent research assistant not involved in recruitment or evaluation will place the random numbers sequentially into sealed, opaque envelopes. Each envelope is individually labeled with a unique consecutive serial number. Eligible patients will be randomly assigned to the verum acupuncture group and the sham acupuncture control group at a 1:1 ratio. The flowchart is shown in Figure 1.

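### The named G*Power t-test needs 17 evaluable per group, not 16, so 20 recruited per group falls slightly short of the stated 80% power after 20% dropout

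*Protocol article*

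**What the plan says.** All the inputs are in the Sample size section of the protocol article. The effect comes from a pilot: "Based on the observed change in itch NRS (numeric rating scale) scores from the pilot experiment", with values "verum acupuncture group: 2.86 ± 1.07 VS sham acupuncture control group: 2.00 ± 0.58". The design targets are "With 80% statistical power, a 5% significance level, and accounting for a projected 20% dropout rate". The method is named as "G*Power software (version 3.1), based on a t-test for the difference between two independent means". The result is "Each group requires 20 people, and a total of 40 subjects need to be recruited". Allocation is 1:1 (Randomization and allocation concealment). The Statistical analysis section says that numerical data "will be analyzed using the independent t-test or Mann–Whitney U test", so the t-test in the calculation belongs to the planned analysis.

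The section does not print the standardised effect, the number of evaluable patients per group before dropout is added, or whether the 5% level is one- or two-sided.

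**The concern.** The article gives inputs, a method and a result, so the result can be checked. A standardised difference close to 1 puts the required size near 16 or 17 per group, where the normal approximation and the exact t-test differ by one patient. The printed total fits the smaller figure, while the text names the test that gives the larger one. What is at stake is whether the stated power is correct under the trial's own assumptions. The conduct of the trial is not affected.

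**Working it through.** **Inputs.** Mean changes 2.86 and 2.00, SDs 1.07 and 0.58, 80% power, 5% significance, 20% dropout, equal groups: all from the article. Two-sided testing is assumed.

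**Effect size.**
- Difference = 2.86 − 2.00 = 0.86.
- Pooled SD = √((1.07² + 0.58²)/2) = √((1.1449 + 0.3364)/2) = √0.74065 = 0.8606.
- d = 0.86/0.8606 = 0.999.

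**Reproducing the printed figure.** Normal approximation, two-sided: n = 2 × (1.960 + 0.842)² × 0.8606²/0.86² = 15.72, so 16 per group. Adding dropout: 16/0.8 = 20 per group, 40 in total. This matches exactly.

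**The named method.** Two-sample t-test with the noncentral t distribution, df = 2n − 2, noncentrality d√(n/2):

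| Evaluable per group | Two-sided power |
|---|---|
| 16 | 0.7808 |
| 17 | 0.8065 |
| 18 | 0.8295 |
| 20 | 0.8685 |

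The smallest n that reaches 0.80 is 17. Adding dropout:
- by division, 17/0.8 = 21.25, so 22 per group (44 in total);
- by multiplication, 17 × 1.2 = 20.4, so 21 per group (42 in total).

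**Power of the design as printed.** 20 × 0.8 = 16 evaluable per group, so power is 78.1%, which is 1.9 points below 80%. The difference detectable with 80% power at 16 per group is 1.024 × 0.8606 = 0.88 points.

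**Other routes to 20.**
- *Rounding of the printed inputs.* Varying the difference from 0.85 to 0.87 and the SDs within their rounding gives 17 or 18 evaluable per group, never 16.
- *One-sided 5% t-test.* This needs 14 evaluable; 14/0.8 = 17.5, so 18 per group. It does not give 20.
- *Simple average of the two SDs.* (1.07 + 0.58)/2 = 0.825, d = 1.042, t-test n = 16, then 20. This matches, but the simple average is not the pooled SD of the two-sample t-test.
- *Rounding 20.4 down to 20.* This also gives the printed number, but it still leaves 16 per group after 20% loss.

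**Unequal SDs.** A simulation with the printed SDs and a Welch test gives about 77.1% power at 16 per group, close to the 78.1% above.

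**The case against.** The strongest reply is that the figure is not wrong in any way that matters. It reproduces exactly under a standard formula. The gap is 1.9 points, and it appears only if the whole projected 20% is lost: with 18 evaluable per group power is 83.0%, and with 20 it is about 87%. The primary outcome is collected within one short session, so losing a full fifth of it would be a pessimistic case. The level is given only as "a 5% significance level"; a one-sided test at 16 per group has 86.8% power, and the shortfall disappears.

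Most of this stands, and it fixes the size of the point. It does not remove it. The article says that 80% holds after allowing for 20% dropout, and names a t-test. Under the two-sided reading that claim fails by one evaluable patient per group. The one-sided reading does not return 20 either, so it does not explain the printed number.

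**Conclusion.** The point holds as a minor correction. With the printed inputs and a two-sided 5% level, the named t-test needs 17 evaluable and 21 to 22 recruited per group. The printed 20 is the normal-approximation answer and gives 78.1% power after 20% loss. This rests on two-sided testing, the pooled SD with equal groups, and the full 20% loss.

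Three stronger readings are tempting, and the article does not support them.
- *The trial is underpowered, and a null result would be misread.* A gap of 1.9 points, turning to about 87% without dropout, cannot carry that.
- *The pilot was tiny and its own result inconclusive.* A reader might work back from the printed means and SDs to 7 patients per arm. The article gives no pilot size. The inference assumes whole-number changes and equal arms; 42 per arm fits both printed pairs as well, and the sham pair alone also fits 13. No confidence interval for the pilot effect should be built on it.
- *Power is far lower because the true effect is smaller.* Power would fall with a smaller effect, but the article offers no smaller value, so any chosen figure would be the reader's own.

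As a side remark only: the 0.86-point effect is a pilot point estimate whose precision is not stated, and the Discussion itself calls the study a pilot.

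**What to change.** Keep 40 patients and replace the power statement in the Sample size section with wording such as:

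*With 16 evaluable per group (20 less 20% dropout), a two-sided 5% t-test has about 78% power for a 0.86-point difference (pooled SD 0.86), and about 87% if all 40 are evaluable; the difference detectable with 80% power at 16 per group is 0.88 points.*

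This makes the sidedness and the evaluable number explicit and brings method and result into agreement. If a one-sided test was intended, the section should say so and the figures should be recalculated. The cost is one sentence and a slightly less favourable stated power; there are no extra patients and no change to conduct or analysis.
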